## Abstract

**Background:**

Dental caries is one of the most common diseases affecting children in Saudi Arabia despite the availability of free dental services. School-based dental screening could be a potential intervention that impacts uptake of dental services, and subsequently, dental caries’ levels. The purpose of this study is to evaluate the effectiveness of two alternative approaches for school-based dental screening in promoting dental attendance and reducing untreated dental caries among primary schoolchildren.

**Methods:**

This is a cluster randomised controlled trial comparing referral of screened-positive children to a specific treatment facility (King Saud University Dental College) against conventional referral (information letter advising parents to take their child to a dentist). A thousand and ten children in 16 schools in Riyadh, Saudi Arabia, will be recruited for the trial. Schools (clusters) will be randomly selected and allocated to either group. Clinical assessment for dental caries will be conducted at baseline and after 12 months by dentists using the World Health Organisation (WHO) criteria. Data on sociodemographic, behavioural factors and children’s dental visits will be collected through structured questionnaires at baseline and follow-up. The primary outcome is the change in number of teeth with untreated dental caries 12 months after referral. Secondary outcomes are the changes in the proportions of children having untreated caries and of those who visited the dentist over the trial period.

**Discussion:**

This project should provide high level of evidence on the clinical benefits of school dental screening. The findings should potentially inform policies related to the continuation/implementation of school-based dental screening in Saudi Arabia.

**Trial registration:**

ClinicalTrials.gov, ID: NCT03345680. Registered on 17 November 2017.

## Background

Dental caries is one of the most common diseases affecting children in Saudi Arabia despite the availability of free dental services. The combination of the large burden of untreated caries among schoolchildren, low uptake of dental services when asymptomatic and the availability of free dental services makes Saudi Arabia a unique setting for evaluating school-based dental screening. Despite the availability of free dental services provided through the Ministry of Health, universities’ hospitals and health services of the Ministry of Defence, most Saudis visit the dentist only when in pain [1, 2]. Given the cultural and social norms related to symptomatic dental visits and the availability of free dental services, screening and referral of schoolchildren could be an effective intervention to promote asymptomatic dental visits and to tackle the burden of dental caries [3]. It is also an opportunity for targeting a large portion of the population with a high level of disease as a quarter of the Saudi population is younger than 15 years [4, 5]. School-based dental screening allows early contact of children with the dentist, and may subsequently, promote better compliance of children and their parents [6], which might lead to motivating asymptomatic visits, early detection and timely intervention [2].

Two recent systematic review concluded uncertainty of either harm or benefit of school-based screening in improving children’s oral health or dental attendance [7, 8]. Most of the seven randomised controlled trials (RCTs) identified among the two reviews were of high or uncertain risk of bias, especially in relation to randomisation (no allocation concealment), blinding (lack of blinded outcome assessment) and attrition (incomplete outcome data) [9–14]. The only high-quality study was conducted in the United Kingdom (UK) [15]. This was also the only RCT that examined clinical outcomes (untreated dental caries) rather than just dental attendance. The fact that around 50% of children with untreated caries referred to a dentist received treatment for the referred condition [15] suggests that dental attendance does not provide sufficient information to assess the clinical benefits of school-based dental screening. Another salient methodological issue is that most RCTs looked at short-term effects (3 to 8 months) [7, 8]. A longer follow-up period might be needed to detect clinical changes.

All seven RCTs had a limited scope to dental screening, merely devoted to providing information to parents [7, 8]. No further attempts for follow-up communication and/or provision of assistance to parents with booking appointments was included [9–15]. A successful screening programme requires more than just the screening test; it should have a supporting system to ensure that those needing treatment are able to obtain it [6, 16, 17]. The provision of free dental services does not solve the problem as shown in the UK studies [9–11, 13, 15]. These extra efforts and costs to facilitate contact of screened-positive individuals with health services must be balanced against potential gains (clinical benefits) of the screening programme. Given the above reasons, it was not surprising that systematic reviews concluded that there is a need to conduct a well-designed trial with an intensive follow-up group [7, 8]. The present trial addresses these gaps in knowledge and methodological challenges.

The primary aim is to evaluate the effectiveness of two alternative approaches for school-based dental screening (referral to a specific treatment facility versus current practice —i.e. an information letter advising parents to take their child to a dentist—) in promoting dental attendance and reducing untreated caries among primary schoolchildren in Saudi Arabia. A secondary aim is to determine the effectiveness of school-based dental screening among population subgroups (two subgroups will be specifically considered, namely children who were screened positive and children who reported being regular attenders at baseline).

## Methods

This manuscript adheres to the Standard Protocol Items: Recommendations for Interventional Trials (SPIRIT) 2013 Statement [18] for reporting of protocols for clinical trials and the Consolidated Standards of Reporting Trials (CONSORT) 2010 Statement – extension for cluster randomised trials [19].

### Trial design

This will be a cluster randomised, assessor-blinded, superiority trial with two groups running in parallel and an allocation ratio of 1:1. The trial will be conducted over 12 months, from baseline to follow-up outcome assessments. Randomisation at cluster level (school) will prevent contamination that could arise from delivering both interventions in the same school (i.e. randomisation at child level) while also accounting for variations between schools and areas in which the schools are located.

The trial is sponsored by King’s College London. It is a PhD project carried out by the principal investigator (HA) and supervised by WS and EB. The progress of the study will be closely monitored by a PhD Committee (acting as a Trial Steering Committee), including the principal investigator, the two supervisors and two independent external examiners.

### Setting and participants

The trial will be conducted across 16 primary schools in Riyadh city, Saudi Arabia. A list of all governmental primary schools in Riyadh city, Saudi Arabia, will be obtained from the Ministry of Education and stratified according to area (schools located in high-socioeconomic and low-socioeconomic areas). Schools with in-house dental clinics and participating in any dental screening/preventive programme will be excluded from the trial.

Children in selected primary schools will be considered eligible to join the trial if they meet all inclusion criteria and none of the exclusion criteria.

#### Inclusion criteria

Children aged 6 to 11 years (1st to 5th grade at school) at baselineBoth Saudis and non-SaudisChildren for whom the person with parental responsibility has signed the consent form

#### Exclusion criteria

Children in 6th grade (12-year-olds) as they would have left schools by the time of the follow-up assessment (12 months later)Children with any medically compromised condition such as congenital heart disease, haematological conditions, immune deficiency disease and end-stage renal diseaseChildren who refuse to participate (assent) in the study

### Trial interventions

Children in both groups will be examined for dental caries. The difference between the two trial groups lies in the referral mechanism. A comparison against no intervention was disregarded due to ethical concerns (children would be examined and not informed of their oral problems). Those having untreated dental caries according to the World Health Organisation (WHO) [20] criteria will be considered screened positive and referred according to their allocated group. All others will be considered screened-negative and will not receive a referral.

After dental examinations, screened-positive children in the intervention group will be referred to a specific hospital for treatment (referral to a specific treatment facility), King Saud University Dental College (KSU-DC). Referral to this specific institution is one of the innovations in the proposed research. The triage unit at KSU-DC will provide any urgent care needed and make an appointment for subsequent care. All treatments will be provided free of charge. Screened-positive children in the comparison group will receive the currently accepted practice for school-based dental screening; that is, a letter will be sent to parents informing them of the child’s dental problem and advising to take them to a dentist (conventional screening). For both groups, referral letters will be sent to parents through children’s school bags.

### Trial outcome

Combining clinical and self-reported outcomes will provide more robust evidence on the effectiveness of school-based dental screening. While self-reported dental visits are a direct indicator of the impact of the intervention, they are a surrogate measure of clinical status and subject to measurement bias. We have, therefore, chosen a clinical measure as primary outcome as it will confirm that a dental visit occurred during the trial period. A clinical measure also allows a blinded outcome assessment (caries examination), something that could not be achieved with self-reported dental visits as participants will know which group they are in.

#### Primary outcome

The study primary outcome is the change in the number of teeth with untreated dental caries in both primary and permanent teeth over 12 months. The underlying assumption of the selected primary outcome is that students in the intervention group will visit a dentist during the trial period and as a result will have fewer untreated decayed teeth than those in the comparison group. While the use of a clinical outcome might be perceived more sensitive to services provided after referral, its use is deemed appropriate for this trial as the students will be referred to a specific institution with a system in place to handle those referred.

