There will be 12 dentists doing the fieldwork under the supervision of the principal investigator. Each fieldwork team will consist of an examiner who will perform clinical examinations and a recorder who will register codes in examination forms. Individuals will switch roles to minimise visual fatigue. They have been trained and calibrated before the beginning of the trial. Mean Kappa values for inter- and intra-examiner reliability in caries diagnosis at tooth level were 0.78 and 0.86, respectively. The principal investigator will hand over referral letters to screened-positive children in girls-only schools (instructing them to put them in the school bags and taking them to their parents). A male organiser, who will not be involved in dental examinations, will do the same in boys-only schools.

Clinical examinations for dental caries will be performed according to WHO criteria that defines dental caries at the caries into dentine threshold [20]. No radiographs will be taken. Examinations will be conducted similarly at baseline and follow-up, with children sitting on a school chair, using headlamps, plane mouth mirrors and a periodontal probe. Teeth will not be brushed or professionally cleaned before examination but cotton wool rolls/buds and the periodontal probe will be used, respectively, to dry the surfaces and remove moisture/debris to facilitate visual inspection. Standard infection control measures will be in place.

After clinical examinations at baseline and follow-up, 10% of participants will be re-examined by the same fieldwork team to assess intra-examiner reliability. After clinical examinations in the follow-up assessment (at 12 months) screened-positive children in both trial groups will be referred to KSU-DC (close-out procedure).

Given the training and calibration of examiners in caries assessment, the probability of having false-positive cases is minimal. Upon referral, a standard dental check-up is always conducted as part of the treatment plan where any false-positive cases will be identified. If that occurs, the dentist will inform parents that upon further examination no treatment is required.

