### Data analysis

#### Justification of sample size

Based on a previous relevant study [15], a sample size of 910 children (455 in each trial group) is required to detect a 0.50-unit difference in the number of teeth with untreated caries between the conventional screening group and specific screening group, assuming 80% statistical power, 5% significance level and intra-class correlation coefficient (ICC) for dental caries at school level of 0.03. The total sample size will be rounded up to 1010 (505 in each group) to allow for a dropout rate of up to 11%. After compensating for the clustering of children within schools, there will be six clusters per group, each cluster will include at least 75 participants.

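### The primary outcome counts a decayed primary tooth that is shed naturally as if it had been treated, so a fall in the count does not confirm a dental visit and the absolute effect is somewhat diluted

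*Protocol article*

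**What the plan says.** All references are to the protocol article.

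- **Primary outcome:** the "change in the number of teeth with untreated dental caries in both primary and permanent teeth over 12 months". The mechanism given for a group difference: "students in the intervention group will visit a dentist during the trial period and as a result will have fewer untreated decayed teeth".
- **Trial outcome:** the authors have "chosen a clinical measure as primary outcome as it will confirm that a dental visit occurred during the trial period".
- **Inclusion criteria and Trial design:** children are 6 to 11 years old at baseline, and "The trial will be conducted over 12 months, from baseline to follow-up outcome assessments".
- **Data collection:** "Clinical examinations for dental caries will be performed according to WHO criteria that defines dental caries at the caries into dentine threshold". The method is the same at both visits, codes are recorded on examination forms, and examiner agreement is reported at tooth level.
- **Secondary outcomes:** one is the change in the proportion of children with any untreated caries.
- **Justification of sample size:** the trial is sized "to detect a 0.50-unit difference in the number of teeth with untreated caries".
- **Between-group comparisons:** age is compared between groups, but the adjustment sentence names only socioeconomic and behavioural differences.
- **Supplemental analysis:** results will also be given separately for primary and permanent teeth.
- **Discussion:** more visits without a clinical difference will be read as a problem with services, not with the screening tool.

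Natural shedding of primary teeth is not mentioned anywhere, and nothing separates a decayed tooth that was treated from one that fell out.

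**The concern.** The count is net and covers both dentitions at ages when primary teeth are being replaced. Suppose a child has three decayed primary teeth, sees no dentist, sheds all three and develops no new lesion. That child scores -3, the same as a child whose three teeth were all filled. The count therefore cannot do what the Trial outcome section says it does.

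The practical stake is sensitivity. A decayed tooth that would have been shed by 12 months anyway cannot show a benefit of referral at 12 months. Dental attendance is not diluted in this way. Shedding thus pushes results towards more visits with little clinical difference, which is the pattern the Discussion would attribute to services.

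Shedding also depends on age. With six schools per group (sample size section) or 16 in all (Setting and participants), a chance difference in age mix between groups can move the net count, and age is not named for adjustment.

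**Working it through.** **1. Does a fall in the count imply a visit?** The definition has no rule for a tooth that is absent at follow-up, so a shed decayed tooth and a treated one each contribute -1. The converse also fails: the Background reports that only around 50% of referred children with untreated caries in an earlier trial were treated for that condition, so a visit can leave the count unchanged. This step needs no assumed rate.

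**2. The plan's own sample size.** Stated inputs: difference 0.50, power 80%, significance 5% (taken as two-sided), ICC 0.03, 75 children per cluster, 455 per group. No SD is given, so 455 cannot be reproduced from stated inputs alone.

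- Design effect = 1 + (75 - 1) × 0.03 = 3.22.
- Effective n per group = 455 / 3.22 = 141.3.
- Implied SD = 0.50 × √(141.3 / 2) / (1.960 + 0.842) = 1.50.
- Forward check: n = 2 × (1.960 + 0.842)² × 1.50² / 0.50² = 142 after rounding up; 142 × 3.22 = 457, close to 455.

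**3. Illustrative dilution.** Let s be the share of all baseline-decayed teeth shed within 12 months. It is an assumption, as the article gives no figure. Take 0.50 as the effect without shedding, hold the SD at 1.50, and use difference = 0.50 × (1 - s).

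| s | Difference | Power at 455 per group | n per group for 80% power |
|---|---|---|---|
| 0 | 0.50 | 80% | 458 |
| 10% | 0.45 | 71% | 564 |
| 20% | 0.40 | 61% | 712 |
| 30% | 0.35 | 50% | 931 |

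If the 910 children are instead spread over 16 schools (56.9 each, design effect 2.68), the powers are 87%, 79%, 69% and 58%.

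**4. Absolute and relative scales.** Assume a mean of 3.3 decayed teeth, visits in 20% (comparison) and 35% (intervention) with full treatment at a visit, and 0.5 new lesions per child.

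- Expected follow-up count = 3.3 × (1 - visit rate) × (1 - s) + 0.5.
- s = 0: 3.14 and 2.645; difference 0.495, ratio 0.842.
- s = 30%: 2.348 and 2.0015; difference 0.347, ratio 0.852.

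The absolute difference shrinks by the factor (1 - s), while the ratio of follow-up counts hardly moves. Simulating the same set-up gave differences of 0.50, 0.44, 0.39 and 0.35 at s = 0, 10%, 20% and 30%. Among comparison children whose count fell, 49% (s = 10%) to 69% (s = 30%) had made no visit.

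**5. Dependence on the analysis form.** A second simulation of this kind, with an overdispersed baseline count, compared s = 0 with s = 20%. On the raw change score, the standardised difference fell from 0.187 to 0.156. Adjusted for the baseline count, it fell only from 0.206 to 0.199. When shedding depended on age, the corresponding falls were 0.199 to 0.151 and 0.219 to 0.189.

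**The case against.** **The strongest case against.** Net untreated decay is a legitimate measure of disease burden. Randomisation makes shedding similar between groups in expectation, so it creates no false effect. The planned primary model yields a rate ratio, which barely moves. The planned permanent-tooth comparison is free of shedding. The previous study behind the sample size also measured untreated caries, so 0.50 may already include shedding. Tooth-level coding and covariate lists are often left to an analysis plan.

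**What stands.** All of this limits the size. It does not rescue the statement that the outcome "it will confirm that a dental visit occurred during the trial period", which is a positive assertion in the article and not a detail left to another document. The trial is sized on an absolute difference, and absolute differences will be reported. The permanent-tooth comparison does not repair the primary-tooth count or the combined primary outcome.

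**Stronger readings that the article does not support.**

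- A reader might assume 2 to 4 decayed primary teeth per child with 15% to 35% shed, obtain a natural loss of 0.3 to 1.4 teeth, and set that against the 0.50 target. That compares a shift within each group with a difference between groups; the shift largely cancels.
- A reader might conclude that a true 0.50 becomes 0.33 to 0.43. That requires 0.50 to exclude shedding, which the article does not say, and it applies those same assumed shares to the whole effect.
- A reader might expect shedding to inflate the variance in general. In the second simulation the SD of the follow-up count fell, from about 3.6 to 3.0 at s = 20%; on the change score it was flat or slightly higher.

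**Conclusion.** The point holds as one of interpretation and sensitivity. The net count falls through natural shedding as well as through treatment, so the sentence saying it confirms a visit is wrong as written. The any-caries secondary outcome is affected too, whenever the last decayed tooth is shed.

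The harm is not bias under the null. It is some attenuation on the 0.50-tooth scale, age-related noise, exposure to chance age imbalance with few schools per group, and a clinical null that the Discussion's rule could wrongly attribute to services.

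The size cannot be taken from the article. The fall in power to 71%, 61% or 50% rests on assumed shedding of 10%, 20% or 30%, a back-solved SD of 1.50 held constant, and a 0.50 that excludes shedding. If 0.50 already reflects shedding, the loss is smaller or nil. With adjustment for the baseline count, or on the ratio scale, the effect of shedding is smaller than the change-score figures suggest.

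**What to change.** Keep the net count as the primary outcome and make four changes:

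1. **Covariate.** Name baseline age or grade as a prespecified covariate in the primary and secondary outcome models. Age is already collected.
2. **Supporting outcome.** From tooth-level codes at both examinations, take teeth decayed at baseline that are not due to shed within 12 months, under a fixed age rule per tooth type. Permanent teeth all qualify. Count those filled or extracted at follow-up, and report new lesions separately.
3. **Trial outcome wording.** Replace the claim of confirmation with a statement that the net count also falls through natural shedding.
4. **Discussion.** Carry the same caveat into the rule for reading more visits without a clinical difference, and consult the supporting outcome before attributing that pattern to services.

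**Cost.** Wording, a tooth-type rule and some programming, with no extra examinations provided codes are kept by tooth. Extraction and shedding cannot always be told apart, some primary teeth drop out of the supporting outcome, and it measures treatment received, not disease burden. That is why it should support the net count and not replace it. On the article's dates (recruitment to April 2018, follow-up at 12 months), the rule could be fixed before follow-up data exist.

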#### Secondary outcomes

The change in the proportion of children having teeth with untreated caries and the change in the proportion of children who reported visiting a dentist (as reported by parents and children) during the duration of the trial will be the secondary outcomes.

